#### Microbial abundance and diversity

For the gut, skin, and oral microbiomes, we will compare microbial abundance at the baseline and end of the trial across different treatment arms to investigate how cannabis oil treatment affects pain assessment. The alpha and beta diversity of the microbiota will be analyzed.

#### Determination of pharmacokinetic and pharmacogenetic parameters

The kinetic concentrations of THC and CBD will be quantitatively measured in two visits to determine the pharmacokinetic and the candidate genes for pharmacogenetic parameters.

### Safety

It has been confirmed the effectiveness of the cannabis products in the preliminary analysis and monitored the side effect at the trials.

### Statistical considerations

#### Sample size estimation

We target 30 patients in each arm, considering the maximum follow-up loss of 50%. Since the target population is metastatic breast cancer cases, questionnaires and biological samples such as blood, stool, saliva, and breast skin scrapping will be collected before and after the treatment, which could increase the withdrawal rate at any time during the trial.

#### Statistical analysis

The data collected from different questionnaires, including case report forms, will be prepared in Microsoft Excel, followed by data cleaning and extraction. The statistical analysis will be performed on an intention-to-treat basis using Stata/MP software version 16.0 (StataCorp 2017, College Station, TX). Descriptive statistics like pair t-tests for before and after-treatment groups will be carried out using mean with standard deviation for normally distributed continuous data and median with interquartile range for non-normal distributed continuous data. Categorical data will be presented as counts and percentages using the Chi-square test. Continuous data will be assessed for normal distribution using a histogram and Shapiro–Wilk test. One-way ANOVA with Bonferroni correction will be used for normally distributed continuous data, and the Kruskal-Wallis test will be used for non-normal distributed continuous data among 3 arms.

To identify the alpha diversity, Shannon’s diversity index is used for evenness and Chao 1 index for the richness of operational taxonomic units (OTUs). The Jaccard dissimilarity index is used to detect beta diversity, and it is statistically described by permutational multivariate analysis of variance using distance matrices (PERMANOVA) test. A statistically significant level is defined as *p* < 0.05. Correction for multiple analyses was not done, but they will not be included in the conclusion of the study as factual findings. Sensitivity analysis using some subgroup to show robustness will be considered if the primary outcome is statistical significance.

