## Materials and methods

### Target population

We include 90 adult breast cancer women patients who were diagnosed with breast cancer or currently receiving chemotherapy at King Chulalongkorn Memorial Hospital (KCMH) with an anticipated starting recruitment approximately in August 2023. The sample size was calculated using the mean ESAS values of the previous study [29].

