#### Patient allocation and blinding

The recruited patients will be randomly allocated into 3 groups: Ganja Oil (THC 1.701 mg/mL or 0.068 mg/drop; CBD 0.003 mg/mL or 0.0001 mg/drop; CBN 0.170 mg/mL or 0.007 mg/drop; COA Ganja Oil TRCM65/05232), Metta Osot (THC 77.622 mg/mL or 3.105 mg/drop; CBD 6.737 mg/mL or 0.2695 mg/drop; CBN 7.406 mg/mL or 0.296 mg/drop; COA Metta Osot TRCM64/33,743 Rev.1), and placebo oil (THC 0 mg/mL or 0 mg/drop; CBD 0 mg/mL or 0 mg/drop; CBN 0 mg/mL or 0 mg/drop; COA Placebo TRCM64/33,742) groups. The allocation will be conducted with a 1:1:1 ratio using block randomization with a block of six by the table of random numbers for creating randomization ID. The research team will provide the randomization code in an opaque envelope to conceal allocation, mask clinicians, data collectors, and patients. Following the cannabis practice patterns of the preliminary study [29], all the participants will be received cannabis or placebo oil once per day before bedtime for 12 weeks.

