#### Trial timepoints

Assessment of adverse drug effects will be collected with 4 time points: 0th, 1st, 6th, 12nd weeks of the trial day. The pain symptoms, QoL and diet pattern will be recorded with 3 time points: 0th, 6th, 12nd weeks. The blood collection (3 mL) for pharmacokinetic and pharmacogenetic tests will be performed on 2 time points: 0th, 6th weeks. The blood (10 mL), feces, skin scrapping, and saliva samples will be taken for biochemistry tests (plasma/ serum), microbiome (gut/ skin/ saliva), cytokines (plasma) and bacterial metabolites (serum/ feces) will be analyzed at 2 time points: 0th, 12nd weeks. The overview of the tests and visits of the clinical trial was shown on the following Table 1.

**Table 1 Tab1:** SPIRIT schedule of enrolment and assessments

#	Timepoint	Week-0 baseline	Week-1 follow-up	Week-6 follow-up	Week-12 follow-up
		T1	T2	T3	T4
1	**Enrolment**				
	Eligibility screening	x			
	Informed consent	x			
	Allocation	x			
2	**Assessment**				
	CRF01 Case Record Form^a^	x			
	CRF02 FW & ADR^b^	x	x	x	x
	CRF03 ESAS	x		x	x
	CRF04 EQ-5D-5 L	x		x	x
	CRF05 Food Frequency Questionnaire	x		x	x
3	**Blood Samples, Serum**				
	Blood Chemistry^c^	x			x
	Cytokines^d^	x			x
	Bacterial Metabolites^e^	x			x
	Pharmacokinetics parameters	x		x	
	Pharmacogenetics parameters	x		x	
4	**Feces Samples**				
	Fecal Microbiome Profile	x			x
	Fecal Bile Acid Profile^f^	x			x
	Fecal SCFAs^g^ and BCFAs^h^	x			x
5	**Skin Samples**				
	Skin Microbiome Profile	x			x
6	**Saliva Samples**				
	Oral Microbiome Profile	x			x

^a^Demographic and Epidemiological Factors: age, weight, height, waist circumference, hip circumference, neck circumference, alcohol consumption, smoking status, occupation, monthly income, method of health payment, and highest education

^b^Follow up and adverse drug reaction: vital signs, physical examination, lab results to assess liver, kidney and heart function, pharmacokinetic record form, drug tolerance assessment form, and adverse event assessment form

^c^Blood Chemistry: lipid profile, liver function test (LFT)

^d^Cytokines: interleukin-17, interferon-gamma, Interleukin-10, tumor growth factor-beta

^e^Bacterial Metabolites: lipopolysaccharide binding protein, sCD14 levels, equol, cadaverine

^f^Fecal Bile Acid Profile: chenodeoxycholic acid, deoxycholic acid, lithocholic acid

^g^SCFAs: butyric acid, propionic acid, acetic acid

^h^BCFAs: iso-butyric acid

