### Primary outcome measures

The pain level of each patient will be assessed using the ESAS form at the last visit as primary outcome.

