### Secondary outcome measures

#### Pain level assessment

The ESAS at 0^th^, 6^th^ weeks visits will be taken as secondary outcome measures and will be evaluated all the symptoms.

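### The only sensitivity analysis depends on a significant result and does not address missing data, and the named tests do not by themselves deliver intention-to-treat when week-12 pain is missing

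*Protocol article*

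**What the plan says.** All of the following is in the protocol article.

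- **Analysis basis** (Statistical analysis): "The statistical analysis will be performed on an intention-to-treat basis using Stata/MP software version 16.0". The same section names one-way ANOVA with Bonferroni correction, or Kruskal-Wallis, for continuous data across the three arms, and paired t-tests before and after treatment.
- **Primary outcome** (Primary outcome measures): "The pain level of each patient will be assessed using the ESAS form at the last visit as primary outcome". Visits and follow-ups identifies the last visit as week 12.
- **Other pain scores** (Trial timepoints): "The pain symptoms, QoL and diet pattern will be recorded with 3 time points: 0th, 6th, 12nd weeks". Under Pain level assessment, the ESAS scores at weeks 0 and 6 are secondary: those "visits will be taken as secondary outcome measures and will be evaluated all the symptoms".
- **Loss** (Sample size estimation): "We target 30 patients in each arm, considering the maximum follow-up loss of 50" per cent. The section adds that withdrawal could rise at any point because of the questionnaires and sampling.
- **Sensitivity analysis** (Statistical analysis): "Sensitivity analysis using some subgroup to show robustness will be considered if the primary outcome is statistical significance".

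**The concern.** There are two faults, and the first is in the text itself.

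**The sensitivity rule.** Whether robustness is examined depends on the answer. A non-significant result gets no check, although uneven loss can hide an effect as easily as create one. After a significant result the check is only to be considered, so it is not assured even then. The subgroup is not named. In any case, an analysis in a subgroup does not show what missing week-12 scores could have done to the estimate.

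**Intention-to-treat against the named tests.** ANOVA and Kruskal-Wallis on a single time point can use only patients who have a score at that time point. With substantial loss planned for, the comparison would rest on whoever returned at week 12 unless something else is specified. The week-0 and week-6 scores, which carry information on those who left, play no part in the named between-arm tests.

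At stake is the oil-placebo comparison. If the kind of patient who leaves differs between arms, the remaining patients are no longer comparable, and no planned analysis would show it.

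**Working it through.** **1. The plan's own figures.** "We include 90 adult breast cancer women patients", and "The allocation will be conducted with a 1:1:1 ratio using block randomization with a block of six". This gives 90 / 3 = 30 per arm. At the stated maximum loss, 30 × (1 − 0.5) = 15 per arm have a week-12 score, or 45 of 90. In the other direction, 15 / (1 − 0.5) = 30, so the target is consistent with 15 evaluable patients per arm. The article gives no design difference, SD or power, so 15 itself cannot be derived.

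**2. Bias in observed-case means.** Let *p* be the fraction lost in an arm, *C* the mean of those who stay and *D* the mean that those who leave would have had. The full mean is (1 − *p*)*C* + *pD*, so the observed mean differs from it by −*p*(*D* − *C*). With equal *p* in two arms, the between-arm bias has size *p* × [difference between arms in (*D* − *C*)]. At 50% loss, a 1-point difference in that gap gives 0.5 points of bias. If the gap is the same in both arms, the bias is zero.

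**3. Size under assumed mechanisms.** None of these inputs is in the article: SD 2.4; correlations 0.6 (weeks 0 and 6), 0.65 (weeks 6 and 12) and 0.5 (weeks 0 and 12); no true effect; loss depending on week-6 pain in one arm and random in the other. Large-sample simulation gives this absolute bias in the week-12 difference:

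| Loss per arm | Log-odds 0.5 per SD | Log-odds 1 per SD |
|---|---|---|
| 20% | 0.15 | 0.27 |
| 30% | 0.23 | 0.40 |
| 50% | 0.37 | 0.65 |

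A rerun agreed to within about 0.02. With the same mechanism in both arms the bias is zero. With opposite mechanisms at 50% loss and log-odds 1 it is about 1.3, which is an extreme case.

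For scale only, the Introduction (Clinical practice in Thailand) reports a one-month before-after pain change of 0.95 (SD 2.39) in the earlier cohort. The largest one-arm figure is 0.65 / 0.95 = 68% of that, and the smallest is 0.15 / 0.95 = 16%.

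**4. Effect on the test.** A second simulation used 30 per arm, SD 2.39, no true effect and one-way ANOVA on observed scores. Loss depended directly on week-12 pain in both oil arms and was random on placebo.

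- Random loss of 50% in all arms: type I error 0.053.
- 50% loss, correlation between pain and dropout score 0.45: type I error 0.17, bias −0.8.
- 50% loss, correlation 0.71: type I error 0.39, bias −1.3.
- About 25% loss, correlation 0.71: type I error 0.21, bias −0.7.

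**5. What the earlier scores recover.** In the setting of step 3, an estimate using weeks 0 and 6 is within about 0.015 of the truth when every patient who leaves has a week-6 score. That follows from the set-up, because loss then depends only on an observed value. At 50% loss and log-odds 1, if half of those lost leave before week 6, about 0.12 of the 0.65 remains. If all do, about 0.37 remains.

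**The case against.** A reader might infer that the primary analysis is a completers' analysis and that the intention-to-treat statement is therefore false. The article does not say so. It neither states nor excludes a rule for missing scores, and such a rule is commonly left to a full protocol or SAP, neither of which is shown. That objection stands: what can be shown is a conflict that remains unless a rule exists elsewhere.

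Four further points also stand.

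- The 50% is a planning maximum, not an expected loss.
- The only cause of withdrawal that the article gives is the burden of data collection, which all arms share and which need not bias anything. Differential loss is plausible, since the three oils differ widely in THC content and the article lists adverse effects of cannabinoids, but it is conjecture.
- The earlier scores are not ignored altogether. They are secondary outcomes, and before-after tests are planned. A single-time-point primary outcome is a legitimate choice.
- It is tempting to say that the subgroup check can only favour a positive result. It could also undermine one, and the article does not say that the subgroup would be picked after the data are seen, only that it is unspecified.

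None of this rescues the sensitivity sentence. A fuller document could add detail, but it could not keep that condition and also report checks whatever the result.

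**Conclusion.** The point holds in two parts of unequal certainty. The conditional sensitivity rule is a stated fault and needs no assumption: a non-significant result is not examined, and missing data are not addressed whatever the result. The conflict between intention-to-treat and the named tests is real but depends on what an unseen document may say, so the conclusion that the trial will analyse completers only goes further than the article does.

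If no missing-data rule exists, the plausible bias is 0.15 to 0.4 points at 20 to 30% loss, and 0.35 to 0.65 points at the 50% ceiling. These figures rest on the assumed SD, correlations and one-arm loss mechanism. Bias is nil if the mechanism is common to the arms. The 0.95-point comparison is a scale marker from an uncontrolled before-after change, not a design effect that the article names.

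**What to change.** 1. Replace the conditional sentence with wording such as: *Whatever the primary result, sensitivity analyses for missing week-12 pain (for example a delta tipping point) will be reported. Subgroups are listed in advance and are not used as robustness checks.*

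2. Keep week-12 ESAS pain as the primary outcome, but estimate it from a repeated-measures mixed model. Enter pain at weeks 0, 6 and 12 as outcomes, with baseline means constrained equal across arms, and report each oil-minus-placebo difference at week 12. With baseline as an outcome, every randomised patient with a week-0 score stays in the model, including those who leave before week 6. A model limited to patients with a post-baseline score would drop them.

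3. If a missing-data rule already exists in the full protocol or SAP, state it next to the intention-to-treat claim.

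The cost is protocol and SAP wording and modest programming in the software already named, with no new visits or samples. It should be settled before unblinding. The downside is that the model assumes data missing at random and only partly corrects bias from patients who leave before week 6. The tipping-point analysis is there to probe both limits.

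### Free improvement: adjust the primary week-12 ESAS pain comparison for the week-0 pain score, which is already scheduled for every patient

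*Protocol article*

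**What the plan says.** All places are in the protocol article.

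- **Primary outcome measures:** "The pain level of each patient will be assessed using the ESAS form at the last visit as primary outcome". This is a single post-treatment score; no change from baseline is defined.
- **Trial timepoints**, and the ESAS row of Table 1: "The pain symptoms, QoL and diet pattern will be recorded with 3 time points: 0th, 6th, 12nd weeks". A week-0 pain score is therefore scheduled for every patient.
- **Pain level assessment:** the ESAS at the week-0 and week-6 "visits will be taken as secondary outcome measures and will be evaluated all the symptoms". The baseline score is given the role of a secondary outcome, not of a covariate.
- **Statistical analysis**, between arms: "One-way ANOVA with Bonferroni correction will be used for normally distributed continuous data". Where the data are not normal, a rank-based alternative is named instead: "the Kruskal-Wallis test will be used for non-normal distributed continuous data among 3 arms".
- **Statistical analysis**, before against after: "Descriptive statistics like pair t-tests for before and after-treatment groups will be carried out". These tests are called descriptive and do not compare the arms.
- **Target population** and **Sample size estimation:** "We include 90 adult breast cancer women patients"; "We target 30 patients in each arm, considering the maximum follow-up loss of 50" percent.

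**The concern.** Taken together, the outcome definition and the named tests leave week-0 pain out of the primary randomised comparison. A woman's starting pain probably predicts some of her pain 12 weeks later. If it does, leaving it out keeps variation in the error term that a covariate would remove.

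The described design does nothing else to balance starting pain. Allocation is in blocks of six with no stratification mentioned. The inclusion criteria admit any stage, women about to start chemotherapy as well as women already on it, and set no pain threshold. At the planned size, chance differences in starting pain between arms can be appreciable. The stake is a wider interval and a less sensitive test than the scheduled data allow.

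**Working it through.** **1. Evaluable numbers.** 90 / 3 = 30 per arm. With the maximum 50% loss, 30 × (1 − 0.5) = 15 per arm. So 15 to 30 per arm are evaluable.

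**2. Inputs.** The article gives neither a single-visit SD nor rho. Its one pain figure is the one-month change in the earlier cohort, 0.95 ± 2.39 (Clinical practice in Thailand). If the SDs at both visits are equal, the single-visit SD is 2.39 / √(2(1 − rho)):

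- rho 0.3: 2.02
- rho 0.5: 2.39
- rho 0.7: 3.09

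The illustrations below use SD 2.39 and rho 0.5, which are consistent with each other.

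**3. Chance imbalance at baseline.** The SE of the difference in baseline means between two arms is SD × √(2/n). The probabilities use the normal approximation and refer to one given pair of arms.

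| n per arm | SE (in SDs) | P(difference > 0.25 SD) | P(difference > 0.5 SD) |
|---|---|---|---|
| 15 | 0.365 | 49% | 17% |
| 30 | 0.258 | 33% | 5% |

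An imbalance shifts the unadjusted week-12 difference by rho times its size. At 15 per arm and rho 0.5, a one-SE imbalance is 2.39 × 0.365 = 0.87 points and shifts the result by 0.44 points.

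This is not a second harm on top of lost precision. The squared shift, 0.436² = 0.190, is 25% (rho²) of the unadjusted variance 2.39² × 2/15 = 0.762. It is the same part that adjustment removes.

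**4. Gain from adjustment.** The variance of an arm difference is multiplied by about 1 − rho². The equivalent unadjusted n is n / (1 − rho²).

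| Assumed rho | Variance factor | 15 per arm is worth | 30 per arm is worth |
|---|---|---|---|
| 0.3 | 0.91 | 16.5 | 33.0 |
| 0.5 | 0.75 | 20.0 | 40.0 |
| 0.7 | 0.51 | 29.4 | 58.8 |

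These are large-sample factors. With 45 women in all, estimating the slope costs a factor of about 1 + 1/40 = 1.025. The gain in effective sample is then about 1.333 / 1.025 = 1.30, or 30%, at rho 0.5 (not 33%), and about 1.099 / 1.025 = 1.07, or 7%, at rho 0.3 (not 10%).

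**5. Interval width** (SD 2.39, rho 0.5, 95%, no Bonferroni, two-arm t quantile).

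- 15 per arm: 2.048 × 0.873 = 1.79 unadjusted; 2.052 × 0.873 × √0.75 = 1.55 adjusted.
- 30 per arm: 2.002 × 0.617 = 1.24 unadjusted; 2.002 × 0.617 × √0.75 = 1.07 adjusted.

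**6. Power** for an illustrative 0.95-point difference (noncentral t, same SD and rho). The stated Bonferroni correction is taken as two-sided 0.05/3 for three pairwise comparisons.

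- 15 per arm: about 9% unadjusted, 12% adjusted.
- 30 per arm: about 19% unadjusted, 25% adjusted.

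**The case against.** The strongest reply is that this is a condensed article, that covariates are commonly left to the analysis plan, and that ANOVA is never tied to the primary outcome by name. That carries some weight but does not remove the point. The article states an endpoint and names the only between-arm tests for continuous data. Applied to that endpoint, those tests contain no baseline term, so an ANCOVA would depart from the published method rather than fill a gap.

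Three other objections stand and set the limits of the point.

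- **Validity.** A reader might infer that chance imbalance biases the primary test. Over randomisation the unadjusted comparison is unbiased, holds its type I error, and has a standard error that already includes this variation. The gain is in precision, and in protection when a visible imbalance happens to occur.
- **Other outcomes.** A reader might infer the same defect for EQ-5D utility, cytokines and metabolites. The article does not fix a raw week-12 comparison for these. The section on cytokines and bacterial metabolites speaks of alterations and of levels before and after treatment. The microbiome section compares baseline and end of trial across arms. Both named tests could also be run on change scores, and only for primary pain does the outcome definition point to the raw last-visit score.
- **Size.** Rho is assumed. With no pain threshold at entry and women at different points of chemotherapy, a low correlation is plausible. The 0.95 points are a one-month within-patient change in a cohort, not a target difference of this trial.

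**Conclusion.** The point holds for primary ESAS pain, as a free improvement to a valid analysis. As described, the primary comparison leaves a scheduled baseline measurement unused. Using it would cut the variance of an arm difference by about 9%, 25% or 49% at an assumed rho of 0.3, 0.5 or 0.7. That the baseline is unused is read directly from the article; the size of the benefit is not, because it depends on a correlation the article does not give and on an SD borrowed from change scores in an earlier cohort.

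A reader might also infer that adjustment would rescue the trial's power. It would not: in the illustration, power at the Bonferroni level stays at or below about 25% even with all 30 women per arm evaluable.

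**What to change.** Add one sentence to the Statistical analysis section: the primary analysis is an ANCOVA of week-12 ESAS pain on arm with week-0 ESAS pain as covariate, reporting Bonferroni-adjusted differences between arms with confidence intervals. Add that a rank-based ANCOVA or a robust version will be used if residuals are clearly non-normal; this replaces the switch to Kruskal-Wallis for the primary result. Keep the unadjusted ANOVA or Kruskal-Wallis as a supporting analysis.

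Fix this before unblinding, because adjustment chosen after an imbalance has been seen would not be credible. A plain change score is not an equivalent substitute: its variance factor, 2(1 − rho), exceeds 1 when rho is below 0.5 (1.40 at rho 0.3). The same adjustment may be used for other outcomes with a week-0 value, but this point does not require it.

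The cost is the wording. No new data, visits or patients are needed.

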## Conclusions

The clinical trial will provide the efficacy of Thai cannabis oils in breast cancer female patients in Thailand, mainly in alleviating chemotherapy-related side effects. Furthermore, it will obtain secondary factors such as QoL indexes, alteration of microbiome profile, bacterial metabolites, and cytokines before and after using the cannabis oil, pharmacokinetic parameters, and pharmacogenetic profiles.

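### A normality test chooses the between-arm method, and on the Kruskal-Wallis branch a significant primary result need not show that either oil differs from placebo

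*Protocol article*

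**What the plan says.** The primary outcome is defined in the Primary outcome measures section: "The pain level of each patient will be assessed using the ESAS form at the last visit as primary outcome". There are three arms (Ganja Oil, Metta Osot and placebo oil), and "The allocation will be conducted with a 1:1:1 ratio using block randomization with a block of six".

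The Statistical analysis section gives one rule for comparing continuous data between arms:

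- The selector: "Continuous data will be assessed for normal distribution using a histogram and Shapiro–Wilk test". It sets no threshold and does not say whether the check is made per arm, on pooled data or on residuals.
- The two branches: "One-way ANOVA with Bonferroni correction will be used for normally distributed continuous data, and the Kruskal-Wallis test will be used for non-normal" data among the three arms. Bonferroni is attached to ANOVA only. No pairwise step or correction follows Kruskal-Wallis, and the comparisons that Bonferroni covers are not listed.
- The significance level is 0.05 and is not tied to a named comparison.
- After the diversity methods comes the multiplicity statement: "Correction for multiple analyses was not done, but they will not be included in the conclusion of the study as factual findings".
- A subgroup sensitivity analysis is to be considered only if the primary outcome is significant.

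The section names no analysis as primary. That ESAS pain follows this rule is an inference: it is the only between-arm method given for continuous outcomes. The Conclusions section states the aim: "The clinical trial will provide the efficacy of Thai cannabis oils in breast cancer female patients in Thailand, mainly in alleviating chemotherapy-related side effects".

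**The concern.** The efficacy question has two parts: does Ganja Oil differ from placebo, and does Metta Osot differ from placebo? Followed as printed, the plan answers it differently according to a normality test on the outcome data. One branch has a multiplicity correction. The other ends in a single three-arm p-value that does not say which arms differ and gives no oil-versus-placebo estimate. A significant Kruskal-Wallis result would meet the 0.05 criterion and open the door to the subgroup analysis, yet it could come mainly from oil versus oil. That matters here because the two oils are very different products: the Patient allocation and blinding section gives 3.105 and 0.068 mg THC per drop, a ratio of 3.105 / 0.068, or about 46.

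If pairwise tests were then added to interpret the omnibus result, nothing printed says whether they are gated or corrected, and the unscoped no-correction sentence leaves that open.

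**Working it through.** The plan states no error rate beyond the 0.05 level, so there is no figure of its own to reproduce. The check asks what the permitted readings imply.

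**Inputs from the document.** Three arms at 1:1:1. There are 30 per arm with up to 50% loss (Sample size estimation), so 15 to 30 completers per arm. Alpha is 0.05. The only ESAS pain figure is a one-month change of 0.95 with SD 2.39 (Clinical practice in Thailand).

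**Assumptions.** Scores are integers from 0 to 10; the article does not give the range. SD 2.39 is borrowed from the change score. The shape of the week-12 distribution is unknown, so several were tried.

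**1. Familywise error if independent.** The formula is 1 − (1 − α)^k.
- Two tests at 0.05: 1 − 0.95² = 0.0975
- Three tests at 0.05: 1 − 0.95³ = 0.1426
- Two at 0.025: 1 − 0.975² = 0.0494
- Three at 0.0167: 1 − (1 − 0.05/3)³ = 0.0492

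**2. Familywise error by simulation.** There were 8,000 null trials per setting, with 15 and 30 per arm, normal data and a skewed 0–10 score. Shapiro-Wilk on residuals at 0.05 chose the branch.

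| Reading | Two oil-vs-placebo tests | Three pairs |
|---|---|---|
| Bonferroni on both branches | 4.1–4.6% | 3.8–4.3% |
| Bonferroni after ANOVA, ungated uncorrected pairs after Kruskal-Wallis: normal data | 4.3–4.7% | 4.3–4.6% |
| The same, skewed score | 8.7% | 11.5–11.7% |
| No correction on either branch | 8.5–9.3% | 11.6–12.5% |

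The omnibus test, alone or as a gate before unadjusted pairs, gave 4.5–5.1%. ANOVA and Kruskal-Wallis disagreed about p < 0.05 in only 1.8–3.6% of null trials, so the pre-test itself barely affects type I error.

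**3. What a significant omnibus result shows.** Assume a placebo mean of 4, oil means of 2.75 and 5.25, and SD 2.39. Kruskal-Wallis was significant while neither oil differed from placebo at 0.025 in about 33% of trials with 15 per arm and about 29% with 30 per arm. The oils are 5.25 − 2.75 = 2.5 points apart, but each is only 1.25 from placebo, so the omnibus test responds chiefly to oil versus oil.

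**4. How often the Kruskal-Wallis branch is used.** With rounded, clipped normal scores, Shapiro-Wilk on residuals rejected in 10–32% of trials at mean 4 and 95–100% at mean 1.5. The rate also changes between 15 and 30 per arm, so dropout influences which method is used.

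**5. Cost of a fixed two-contrast rule.** Power from the noncentral t with SD 2.39 and illustrative differences that are not in the document:

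| Setting | Dunnett (about 0.027 per test) | Bonferroni, two (0.025) | Bonferroni, three (0.0167) |
|---|---|---|---|
| 15 per arm, 2.5 points | 72% | 70% | 64–65% |
| 30 per arm, 2 points | 84% | 83% | 79% |

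At the documented 0.95 points, Dunnett gives 12.5% and three-way Bonferroni 9.0% with 15 per arm, and 24.5% and 19.0% with 30 per arm. The choice of correction does not rescue power at that difference.

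**The case against.** The strongest reply is that little here is wrong as opposed to unstated.

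- **The correction statements need not conflict.** Bonferroni is attached to the comparison among arms. The no-correction sentence follows the diversity analyses and keeps the affected results out of the conclusion. A natural reading is correction across arms and none across exploratory analyses. This stands: a reader might infer a flat contradiction, but the text shows only an unscoped sentence.
- **No inflated error is prescribed.** The plan does not call for pairwise tests after Kruskal-Wallis. If the omnibus test gates them, with three arms the procedure is closed; a simulation with one arm different gave 4.7–4.9% error for the pair that was truly equal. This also stands, so error of 9–12% cannot be read as the plan's own rate.
- **The score distribution is unknown.** A reader might infer that ESAS pain has many zeros and will nearly always go to Kruskal-Wallis. The article gives no distribution, and at mean 4 that branch was chosen in at most about a third of trials.
- **Bonferroni over all three pairs is not stated.** A charge that power is spent on oil versus oil therefore rests on an assumption.
- **Biomarkers.** The chance of a false positive across many biomarker tests is a weak point, because uncorrected results are already barred from the conclusion.
- **An analysis plan may name the contrast.** It may, and leaving that to it is ordinary. But the data-driven selector and the one-branch correction are printed in the protocol, so they need amending rather than merely supplementing.

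**Conclusion.** The point holds in a limited form. The printed rule lets the data choose between a corrected ANOVA and an omnibus test with no pairwise step. On the second branch, a significant primary result does not by itself identify an oil that differs from placebo. The size of that gap is about 30% of trials under the deliberately unfavourable assumption that the oils fall on opposite sides of placebo. Their differing THC content makes unequal effects plausible but does not establish that pattern.

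Type I error is not shown to be inflated by what is written. It is about 5% for an omnibus or gated reading, and reaches about 9% (two comparisons) or 12% (three) only if ungated, uncorrected pairs are added. The normality gate does little harm to error by itself; the harm lies in an inference that differs by branch and a primary contrast that neither branch fixes. How often the problem arises cannot be determined without the week-12 score distribution. It should be corrected, though it does not make the trial uninterpretable.

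**What to change.** Amend the Statistical analysis section before unblinding:

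1. Remove the normality gate for the primary outcome.
2. Prespecify two week-12 contrasts in ESAS pain, Ganja Oil versus placebo and Metta Osot versus placebo, from one model adjusted for week-0 ESAS pain (already collected), with robust or bootstrap confidence intervals.
3. Control the family at 0.05 by Dunnett or by Bonferroni for two comparisons. Their power differs by only one to two points in the settings above, so either will do.
4. Make oil versus oil a secondary comparison.
5. Limit the no-correction sentence to secondary and exploratory analyses, and label them as such.

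The cost is protocol and analysis-plan wording, with no extra patients or visits. The downside is a slightly stricter per-comparison threshold (0.025 or about 0.027) than uncorrected testing at 0.05.
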